**Ultrasound**:

In our study we followed the ultrasound protocol described by Chen et al. [10] (Table 2), discarding dynamic parameters and adding others based on the most recent literature.

**Table 2 pone.0281221.t002:** Ultrasound protocol.

VARIABLES	DESCRIPTION
General Position	The patient is seated facing the examiner with the forearm resting supinated on a stable surface (for other patients it may be more comfortable to lie face down with the forearm in full pronation). A rolled towel is placed under the wrist to allow 30°-45° extension of the wrist, minimizing the thenar eminence for better transducer glide. The use of a generous amount of gel is helpful. (*)
Nerve cross-sectional area (CSA) in distal forearm	In the transverse axis, in the distal and volar third of the forearm, the pronator quadratus is located between the radius and ulna. The CSA for the calculation of the wrist-forearm index is measured at this level. (**)
CSA at tunnel entrance	At the level of the pisiform the cross-sectional area of the nerve is measured.
CSA at the tunnel exit and mass search	The cross-sectional area of the nerve is measured at the level of the hook of the hamate. At the same time, an anatomical analysis is carried out to look for any space-occupying lesions (accessory lumbricals, tenosynovitis or hidden cysts, etc.).
Longitudinal axis of the nerve at the exit of the tunnel	Rotate the transducer in line with the 3rd metacarpal; nerve compression may show as a notch or change in caliber. The carpal tunnel is also examined for space-occupying masses by short-axis sliding along the full width of the tunnel.
Dynamic test 1: Thenar digital flexion stress test	Compressing a soft object (towel) between the 1st and 2nd finger is visualized transversely and longitudinally; positive result due to flattening of the nerve due to compression of the flexor tendon. No CSA measurement.
Dynamic test 2: Superficial digital flexor digitorum intrusion test	The superficial and deep flexor belly should enter the tunnel with the wrist in hyperextension contributing to nerve compression. No CSA measurement.
Dynamic test 3: Intrusion test lumbrical muscles	To be positive, flexion of the fingers with full grip must enter the tunnel at the muscle belly of the lumbricals compressing the nerve. No CSA measurement.

(*) in our case, the cylindrical gel canister is the one we have positioned under the patient’s wrist to achieve its hyperextension.

(**) it should be noted that for the measurement of the wrist-forearm index we have carried out, based on other publications, the HAG at the entrance of the tunnel between the HAG and 12 cm from the distal crease of the wrist.

### Criteria for discontinuing or modifying allocated interventions {11b}

Not applicable since the intervention comprises a one-time diagnostic procedure.

### Strategies to improve adherence to interventions {11c}

Not applicable since the intervention comprises diagnostic procedure.

### Relevant concomitant care permitted or prohibited during the trial {11d}

No concomitant care was prohibited during the study.

### Outcomes measures {12}

**Primary outcome measure**

**Secondary outcome measure**

**Demographic variables**: sex, age, time of evolution of the clinic, manual dominance, hand affected, body mass index, employment status, type of work (pink, white or blue collar), time worked, triggers of symptoms, what symptoms are relieved with, as well as toxic habits, whether they are smokers (to be answered affirmative or negative) or alcohol consumers (to be answered affirmative or negative).**Electrodiagnostic variables**: motor conduction velocity of the median nerve (calculating distal motor latency and wrist-elbow motor conduction velocity), motor conduction velocity of the ulnar nerve (calculating distal motor latency, lower and upper wrist-elbow motor conduction velocity), orthodromic sensory conduction of the median, ulnar and radial nerve, as well as antidromic sensory conduction of the median, ulnar and radial nerve.**Ultrasound variables**:
The cross-sectional area (CSA), to be performed with linear tracing, measured over the inner border of the epineurium of the median nerve at the level of the entrance and exit of the carpal tunnel. We take the average of 3 consecutive measurements.The range of median nerve thinning understood as the ratio of the transverse and anteroposterior diameters of the nerve in the proximal-medial intracarpal region, at the level of the pisiform.The wrist-forearm index, understood as the ratio of the CSA at the tunnel entrance to the CSA at 12 cm from the distal wrist crease.The flexor retinaculum bulge, which translates an increase in intracarpal pressure. We measure this by tracing a horizontal from the superior pole of the scaphoid to the superior pole of the pisiform, and a vertical from the superior end of the flexor retinaculum to the horizontal.Power Doppler uptake, which determines the hypervascularization of the nerve, especially in the periphery, at the expense of low-flow intraneural vessels. The uptake is at mid-tunnel level, between the pisiform and hamate nerves.The existence of notches in the nerve in the longitudinal ultrasound view, including the entrance, interior and exit of the tunnel.**Boston Carpal Tunnel Questionnaire** (BCTQ), to assess both the symptoms and the subjective functional impact of patients.**Cost evaluation**: To carry out a cost-effectiveness analysis, we will evaluate the costs of the consumables established by the Andalusian Health Service used in both tests and the average time for each of the tests, in order to calculate the cost of the professional when performing each of them.

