## Objectives {7}

**Primary**: To assess the accurancy of ultrasound in the diagnosis of CTS with respect to nerve conduction studies.

Secondary:

To determine the set of ultrasound parameters (ultrasound standards and reference values) that best predict the existence of CTS.To evaluate the relationship between the intensity or degree of involvement between ultrasound findings and nerve conduction studies.To propose a standardised protocol for the study of CTS by ultrasound.To perform a descriptive cost-effectiveness analysis between ultrasound and neurophysiological studies in the diagnosis of CTS.To detect and describe qualitative anatomical alterations and pathological findings that could predispose to the presence of CTS.

**Hypothesis**: Ultrasound is more accurate than neurophysiological studies in the diagnosis of CTS.

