## Trial design {8}

Prospective, cross-sectional study that compares electroneurography and ultrasound in the diagnosis of CTS. Also, a cost-effectiveness analysis will be proposed to evaluate the costs of the consumables established by the Andalusian Health Service used in both tests and the average time for each of the tests, in order to calculate the cost of the professional when performing each of them.

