## Statistical methods

### Statistical methods for primary and secondary outcomes {20a}

After an initial exploration of the data, quantitative variables are expressed as means and standard deviations or medians and quartiles in case of asymmetric distributions, and qualitative variables as percentages.

The calculation of the measures of test accuracy of the ultrasound test as a diagnostic test for CTS: sensitivity, specificity, predictive values and likelihood ratios, are carried out considering the neurophysiological study as the reference test (gold standard).

Likewise, the reliability of the ultrasound is analyzed by calculating the degree of agreement between the diagnoses of the two tests using Cohen’s Kappa coefficient. The concordance of both tests with the established clinical severity is also studied.

The analysis of the quantitative variables did not present normality (Gaussian assumptions), therefore, for statistical inference, the Mann Whitney test (violations of Gaussianity) was used for independent quantitative variables. Shortly afterwards, a multivariate logistic regression model will be created to try to determine the best subset of them that predict CTS [20].

Finally, ROC curves will be performed to evaluate cut-off points for certain quantitative ultrasound parameters that discriminate well against CTS. In the ROC curves, the optimal cut-off point for greater sensitivity and specificity was determined by using the Youden index. In those ultrasound parameters where the ROC curve did not allow adequate discrimination, the median value of the data distribution was used.

In summary, the univariate analysis aims to identify which ultrasound parameters are related to the result of the CTS, thus providing elements of analysis to determine the cut-off points to be evaluated by means of ROC or medians, as well as the main variables to be considered in the multivariate model.

Data analysis is performed with SPSS 25.0 statistical software.

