### Methods for additional analyses (e.g. subgroup analyses) {20b}

Not applicable, no additional analysis will be performed.

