The last two "items" that we analyzed in our study are, on the one hand, the search for anatomical alterations that may compress the median nerve as it passes through the tunnel (ganglions, tendonitis, etc.), since ultrasound allows easy detection of anatomical alterations of the nerve [36]. In our study, as described above, we performed a scan of the image in both the transverse and longitudinal planes, covering all structures from lateral to medial.

On the other hand, we assessed the presence of nerve grimacing in the longitudinal plane, to identify whether there is a specific point of compression. In general, the nerve increases in size immediately after the compression zone.

We have included the BCTQ scale, a validated, self-administered instrument that assesses the impact of CTS on both symptoms and patient function [49], and a statistically significant relationship has been demonstrated between CSA, NPT score, clinical symptoms and hand function [14,15]. Contrary to this, Mondelli et al. in 2008 [16] found no relationship when comparing the combination of ultrasound and NPT score versus BCTQ.

When comparing neurophysiological studies versus ultrasound, although the former offer 85% sensitivity and 95% specificity in the diagnosis of CTS, they are invasive and unpleasant for the patient [12]; recent literature has shown that patients themselves have a preference for ultrasound over nerve conduction studies [49].

Although the specificity of neurophysiological tests is high, there is significant variability in their sensitivity (56–85%) which can translate into false negative results between 10–20% of patients [33] and false positives between 16–34% [50]. Other authors report an NPT sensitivity of 88% and specificity of 93% [44].

Although ultrasound may not replace neurophysiological testing as the gold standard for confirmation, authors Fowler and Gaughan suggest that it could be proposed as a first-line tool [50]; they add that the best candidates for ultrasound are those with high prior probability based on examination and reported symptomatology. Several authors [33,51] propose ultrasound as an initial screening test, leaving nerve conduction for definitive diagnosis.

The use of ultrasound as a diagnostic tool in CTS has many advantages for both the physician and the patient. It is a non-invasive, convenient, and fast tool, and ultrasound equipment is becoming increasingly cheaper, making it more accessible to the healthcare system [21].

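### The analysis labelled cost-effectiveness is defined by costs alone, so as written it is a cost comparison that does not depend on the accuracy of ultrasound

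*Protocol article*

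**What the plan says.** Objectives {7} of the protocol article gives as a secondary objective: "To perform a descriptive cost-effectiveness analysis between ultrasound and neurophysiological studies in the diagnosis of CTS". The Methods part of the Abstract uses the same label.

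Two sections say what the analysis consists of.

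- **Trial design {8}:** "a cost-effectiveness analysis will be proposed to evaluate the costs of the consumables established by the Andalusian Health Service used in both tests", together with the "average time for each of the tests, in order to calculate the cost of the professional when performing each of them".
- **Outcomes measures {12}, in the entry on costs:** "To carry out a cost-effectiveness analysis, we will evaluate the costs of the consumables established by the Andalusian Health Service used in both tests". The second item, professional cost derived from the mean duration of each test, is the same as in {8}.

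Statistical methods {20a} plans sensitivity, specificity, predictive values, likelihood ratios and kappa, with NPT as the reference test. It does not mention cost. Section {20b}, on additional analyses, reads: "Not applicable, no additional analysis will be performed".

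**The concern.** A cost-effectiveness analysis relates a difference in cost to a difference in effect. Both definitions here list cost inputs only. They name no effect (such as patients correctly classified), no ratio and no consequence of a wrong result, although the study will produce the cross-table of ultrasound against NPT that could supply the effect.

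What is at stake is the conclusion drawn on this secondary objective. The Introduction justifies the study partly by a quick and inexpensive technique that would make the health system more efficient. A cost figure published under a cost-effectiveness label would be read as supporting that claim, yet it would contain nothing about how often the cheaper test gives a different answer. The primary accuracy analysis and the sample size are not affected.

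**Working it through.** **Inputs.** Sample size {14}: expected sensitivity 78%, expected specificity 87%, precision 5 points, 95% confidence, 264 NPT-positive and 174 NPT-negative patients, total 438. Discussion: best cited values of 94% and 98%. Introduction: 1 in 5 patients with hand symptoms diagnosed with CTS. The article states no unit costs and no cost-effectiveness figure, so there is none to reproduce.

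**Check of the planning figures.** With n = 1.96² × p(1 − p) / 0.05², p = 0.78 gives 263.7, rounded up to 264, and p = 0.87 gives 173.8, rounded up to 174. The total of 438 reproduces, so the planning values can be used as they stand.

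**Disagreement with NPT.** Let π be the proportion NPT-positive. The proportion that ultrasound classifies differently from NPT is m = (1 − Se)π + (1 − Sp)(1 − π).

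At 78%/87%, m = 0.22π + 0.13(1 − π), which runs from 13% (π = 0) to 22% (π = 1).

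- Quota mix: 0.22 × 264 = 58.1 and 0.13 × 174 = 22.6, so 80.7 of 438 = 18.4%.
- π = 0.2: 0.2 × 0.22 + 0.8 × 0.13 = 14.8%.

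At 94%/98% and the quota mix: 0.06 × 264 = 15.8 and 0.02 × 174 = 3.5, so 19.3 of 438 = 4.4%.

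**What the defined analysis does with this.** Consumables plus professional cost per test contains neither Se, Sp nor π. The result is identical at m = 4.4%, 14.8%, 18.4% or 22%.

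**What an effect term would add.** Assume for illustration only that one ultrasound costs a fraction c of one NPT. The saving per additional patient classified differently from NPT is (1 − c)/m, in units of one NPT cost. At c = 0.5 the cost comparison always reports a saving of 0.5 per patient. The linked figure is:

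- 0.5 / 0.184 = 2.7 at 78%/87%, quota mix
- 0.5 / 0.148 = 3.4 at 78%/87%, 1 in 5
- 0.5 / 0.044 = 11.3 at 94%/98%, quota mix

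The ranking can also change. On cost per patient classified in agreement with NPT, ultrasound is lower only if c < 1 − m: below 0.816 at 78%/87% with the quota mix, 0.852 at 1 in 5, and 0.956 at 94%/98% with the quota mix. A cost-only comparison ranks ultrasound first for every c below 1.

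**Limit of any such figure.** NPT is right by construction here, so every disagreement counts against ultrasound. The article itself reports NPT error. At its figures of 85% sensitivity and 95% specificity, NPT would be wrong in 0.15q + 0.05(1 − q) of patients at true prevalence q, that is 5% to 15%. The Discussion also gives NPT sensitivity of 56–85% and false positives of 16–34%. Part of m may therefore be NPT error.

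**The case against.** The strongest reply is that the Cost evaluation entry lists which costs will be collected, not the whole calculation. The effect side is planned elsewhere: Study setting {9} says the techniques are performed to compare their effectiveness, and {20a} plans the accuracy measures. How the two are combined is detail that an article often leaves to a fuller document. The objective is called descriptive, and accuracy is the primary objective, so readers would see costs beside sensitivity and specificity.

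Part of this stands.

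- The objective is descriptive and has no threshold or adoption rule. A reader might infer that the plan would favour the cheaper test however many patients it misclassifies. The article does not say so.
- The statement in {20b} stands under a heading that gives subgroup analyses as its example. It does not rule out linking cost to accuracy.
- The quotas of 264 and 174 come from two separate precision calculations and do not describe a clinic population, so 18.4% is one point in a range.
- Which cost items to count depends on the perspective taken. A reader might add the missing device cost to the charge, but nothing in the article shows that it would change the comparison.

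The main point is not removed. This is not mere silence: two sections define the analysis, both by the same two cost items, and {20a}, which covers the primary and secondary outcomes, does not connect cost with accuracy. A descriptive cost-effectiveness analysis still needs an effect to describe.

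**Conclusion.** Wrong as written. Carried out as {8} and {12} define it, the analysis is a cost comparison per test and cannot answer the secondary objective in {7}. What it leaves out is a disagreement with NPT of 13% to 22% of patients at the planning values (18.4% at the quota mix, 14.8% at 1 in 5), or 4.4% at the quota mix with the best cited accuracy. These figures rest on the article's expected accuracy and take NPT as correct. The 1-in-5 figure is its general statement about patients with hand symptoms, not a measured prevalence in this clinic. The values of c are assumptions: the Abstract calls NPT expensive, but no prices are given.

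Two further inferences are not supported. A reader might charge one later NPT to each misclassified patient and deduct that from the saving, but misclassified patients cannot be told apart from the others without testing more widely. A reader might also work out how many patients would still need NPT in a screening pathway. The Discussion only reports that several authors "propose ultrasound as an initial screening test, leaving nerve conduction for definitive diagnosis", without saying which ultrasound results would be referred, and the study does not adopt that pathway.

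**What to change.** Choose one of two changes.

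1. **Link cost to accuracy.** In Trial design {8} and Outcomes measures {12}, name an effect measure and how it is combined with cost: for example, the cost saved per additional patient misclassified relative to NPT, with an interval. Compute it from the study's own sensitivity and specificity over a stated range of prevalence, not at the quota mix. Label it as relative to NPT, and add a sensitivity analysis for NPT error using the figures in the Discussion.
2. **Rename it.** Call it a descriptive cost comparison in the Abstract, Objectives {7}, Trial design {8} and Outcomes measures {12}, and make no cost-effectiveness claim.

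The first needs no new patient data, only a few lines of analysis, and may give a less favourable figure for ultrasound. The second costs only wording and narrows the claim.

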### Participant timeline {13}

As shown in Fig 1, we have established a first period for the study, from July 2020 to December 2020, where the initial literature search is carried out, the study protocol is drawn up and submitted to the ethics committee for approval. During this time, a training period is also planned for the researcher in the performance of the ultrasound protocol, a study carried out in the Physical Medicine and Rehabilitation Services of the Virgen Macarena, Virgen del Rocio and Valme University Hospitals, where ultrasound studies are performed on patients with CTS.

**Fig 1 pone.0281221.g001:**
[figure not shown]
Schedule of enrolment, interventions, and assessments.

During the second period of the study, from January 2021 to December 2021, we planned to have performed ultrasound studies on patients. However, due to the Covid-19 pandemic situation, we were forced to prolong this period until September 2022.

We propose a third and final period from September 2022 to May 2023 for data collection, statistical analysis and writing of the study, as well as the relevant corrections.

### Sample size {14}

To calculate the sample size (EPIDAT program) we proposed:

Expected sensibility: 78%Expected specificity: 87%Level of confidence: 95%

In order to evaluate ultrasound as a diagnostic test versus neurophysiological study in patients with a high clinical suspicion of suffering from CTS, expected values of sensitivity and specificity of the ultrasound test of 78% and 87% respectively, a maximum precision of 5% and a confidence level of 95% are considered, resulting in the need to evaluate a minimum of 264 patients with a positive result in the nerve conduction study as well as a minimum of 174 patients with a negative result, which means a total sample of 438 patients (Table 3). The number of positive and negative tests were known because the results were analysed by a secondary investigator. Therefore, the secondary investigator would indicate whether it was necessary to continue appointing patients for ultrasound scans until the total number of patients in both groups were obtained.

**Table 3 pone.0281221.t003:** Sample size.

Precision (%)	Sample Size		
	Positive test	Negative test	Total
5.000	264	174	**438**

The calculation was performed using the EPIDAT software, considering the parameters that underlie the calculation of the required sample size for conducting a diagnostic test evaluation study. The parameters requested by the software are based on sensitivity, specificity, and precision, which were obtained from previous studies.

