In relation to the wrist-forearm index, the first to consider this parameter were Hobson-Webb and his team, who observed that in normal subjects the CSA in the wrist has been described as having the same value as that of the forearm and hypothesized that the ratio between the two could be a diagnostic alternative [29], on this basis, the wrist-forearm index should be 1:1. Both Hobson-Webb et al. [29] and Mhoon et al. [37] observed that values of 1.4 or higher have a high sensitivity (97–100%) to diagnose CTS and values below 1.4 a high sensitivity (99%) to rule it out, the low specificity (28%) limiting its use to screening only.

In our study, based on the approach of Hobson-Web et al. [29], we measured CSA at the tunnel entrance and 12 cm from the distal wrist crease. There are authors who have performed this index using different measurement references [38], so we will not, at the time, establish a comparison between their findings and those of our study. We took 1.4 as the cut-off point, as it is the most frequently considered cut-off point.

In relation to the Doppler tool, its usefulness lies in the fact that in healthy subjects intraneural blood flow has never been demonstrated, which seems to reflect a pathological condition. It has been observed that Doppler can detect increased intraneural or epineural vascular flow in patients with CTS, which seems to reinforce the diagnosis [39], and a correlation has been observed between intraneural flow and CTS severity [40].

When applying the doppler, the position of the wrist is very important, which could also influence blood flow.; the authors Vanderschueren et al. recommend keeping the wrist in a neutral position, avoiding mobilization of the fingers or provocation tests [41].

Another parameter studied over time has been the thickening of the flexor retinaculum in the proximal region of the carpal tunnel, the interest being based on the fact that continued inflammation and the consequent extraneural reactive fibrosis cause a greater thickness of this structure, considered in the pathological range above 1 mm [42]. In any case, in our opinion, like Pardal-Fernández [43], we consider it to be a parameter of low sensitivity, due to the small size of its dimensions and the consequent variability in measurements.

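### The ±5-point precision in the sample size section assumes a cut-off fixed in advance and is not delivered for the ultrasound parameters whose cut-off is chosen in the same patients

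*Protocol article*

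**What the plan says.** Sample size {14} assumes "expected values of sensitivity and specificity of the ultrasound test of 78% and 87% respectively", with "a maximum precision of 5% and a confidence level of 95% are considered". It asks for "a minimum of 264 patients with a positive result in the nerve conduction study" and "a minimum of 174 patients with a negative result, which means a total sample of 438 patients". Table 3 repeats 264, 174 and 438 against a precision of 5.000%. Nothing is allowed for estimating a cut-off.

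Statistical methods {20a} says that "ROC curves will be performed to evaluate cut-off points for certain quantitative ultrasound parameters that discriminate well against CTS" and that "the optimal cut-off point for greater sensitivity and specificity was determined by using the Youden index". For parameters whose ROC curve does not discriminate adequately, "the median value of the data distribution was used". Both rules take the cut-off from the study's own patients. The section mentions no split sample, resampling correction or external validation.

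The Discussion fixes one cut-off beforehand, for the wrist-forearm index: "We took 1.4 as the cut-off point, as it is the most frequently considered cut-off point". For cross-sectional area it cites only a literature range of critical values, 9 to 15 mm², and adopts none. For the retinaculum bulge it hopes to find the best cut-off in this study.

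**The concern.** The formula behind 264 and 174 treats each patient as a yes/no trial under a rule that does not depend on the data. A Youden cut-off does depend on the data: it is the value that makes sensitivity plus specificity largest in this sample. This has two consequences. The cut-off moves from sample to sample and carries sensitivity and specificity with it in opposite directions. And because it was chosen to look best here, the accuracy measured in the same patients is too high on average.

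Accuracy against nerve conduction is the primary objective, and reference values are a secondary one. A reader of {14} and Table 3 would take ±5 points as the reliability of both, including for parameters such as cross-sectional area that have no cut-off fixed beforehand.

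**Working it through.** **1. The plan's own figure.** With n = z²·p(1−p)/d², z = 1.96 and d = 0.05 (inputs from {14}):
- sensitivity: 1.96² × 0.78 × 0.22 / 0.05² = 263.7, rounded up to 264
- specificity: 1.96² × 0.87 × 0.13 / 0.05² = 173.8, rounded up to 174
- total: 264 + 174 = 438

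All three match. With a fixed cut-off, the half-width at these numbers is 5.0 points for each measure, by formula and by simulation.

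**2. The planned cut-off rule.** Each simulated study has 264 reference-positive and 174 reference-negative patients. The Youden cut-off is chosen and evaluated in the same patients. The documents give no marker distribution, so one must be assumed. The main case is binormal: negatives N(0, 1), positives with mean 2.21 and SD 1.40 (AUC 0.90), so that the population Youden optimum is exactly 78%/87%. Mean apparent accuracy is about 79% and 88%.

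The answer depends on what is being estimated:

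| Binormal case | Sensitivity | Specificity |
|---|---|---|
| **Target: accuracy at the population-optimal cut-off** | | |
| 95% half-width (1.96 SD) | ±8.8 | ±8.2 |
| Coverage of nominal 95% Wald interval | 68% | 69% |
| **Target: true accuracy of the cut-off actually chosen** | | |
| 95% half-width of the error | about ±4.9 | about ±4.8 |
| Optimism (points) | about +1.2 | about +1.5 |
| Coverage of nominal 95% Wald interval | 91% | 87–88% |

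**3. Sensitivity to the assumed distribution.** For the first target:
- Other continuous models (logistic, t with 4 df, Gumbel, gamma, equal-variance binormal) stay at or below about ±9. Across all the continuous models the half-widths run from ±7.7 to ±8.8 for sensitivity and ±7.3 to ±9.0 for specificity. The equal-variance model has its optimum at 82.9%/82.9%; the others are set to 78%/87%.
- Rounding the marker values raises both to at most ±9.7.
- In round figures: ±8 to ±10 for sensitivity and ±7 to ±10 for specificity.

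For the second target the half-widths run from about ±4.5 to ±4.9 and ±4.7 to ±5.3, with similar optimism in every model.

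**4. What would restore the precision.**
- In the binormal case, about ±5 at the optimal cut-off needs roughly 4 to 5 times the sample (4 × 438 = 1,752; 5 × 438 = 2,190).
- Holding back half the patients for validation gives 1.96 × √(0.78 × 0.22 / 132) = 7.1 points, and the same for specificity with 87 patients.
- A percentile bootstrap that re-selects the cut-off in every resample (400 simulated studies, 300 resamples each) covered the accuracy at the optimal cut-off in about 96% of studies for each measure, with mean half-widths of about 8.5 and 7.8 points.

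The sample-median fallback was not simulated. It is also taken from the data, but these figures describe the Youden rule only.

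**The case against.** **The arithmetic is right.** This stands. The issue is the match between {14} and {20a}, not a wrong number.

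**The wide figures depend on the target.** A reader usually wants the accuracy of the cut-off that is published, and for that the spread stays near ±5. This stands. One might infer that ±5 holds only for a pre-fixed cut-off, or that 264/174 simply deliver ±9 and ±8. The documents support neither. The first overlooks the reported-cut-off target, where what is lost is 1 to 1.5 points of optimism and some coverage. The second presents an assumed marker distribution as a planning fact. Nominal 95% is nevertheless missed on both targets, and a study that seeks standard reference values has good reason to care about the optimal cut-off.

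**The scope is limited.** This stands too. The ROC step covers certain quantitative parameters. The wrist-forearm index is fixed at 1.4, so the binomial calculation can serve it if its accuracy matches the assumed values. Doppler uptake and notches are described without a measured quantity, so no ROC cut-off is evident for them. Nor does {20a} say that the ultrasound test in its accuracy paragraph is a Youden-dichotomised parameter. It gives no other rule for calling ultrasound positive either, which is why fixing one beforehand is among the remedies.

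**No interval method is stated.** An article may leave this to the full protocol or analysis plan, and its absence is not criticised here. The Wald coverage only shows what the ±5 calculation implies. The precision and the cut-off rule are both stated, and they do not fit each other.

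**Conclusion.** The point holds in this form. The numbers in {14} and Table 3 are correct for a positivity rule fixed in advance, but they do not describe estimates at cut-offs chosen by the Youden index in the same patients. Around accuracy at the optimal cut-off, the 95% half-width is about ±8 to ±10 points for sensitivity and ±7 to ±10 for specificity. In the binormal case a nominal 95% Wald interval covers it in about 68% of studies. For the cut-off actually reported, the half-width is near ±5, the optimism is about 1 to 1.5 points in each measure, and coverage is about 91% and 87–88%.

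The size rests on assumed marker distributions, nearly all with their optimum at 78%/87%. The direction does not depend on which of them is used. The mismatch is worth correcting because it affects how far the main accuracy results and the reference values can be trusted. It does not show that the study is too small to be useful.

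**What to change.** **Sample size {14} and Table 3.** State that ±5 points applies to a cut-off fixed before the data are seen, such as 1.4 for the wrist-forearm index. For Youden-selected cut-offs give about ±8 to ±10 points (sensitivity) and ±7 to ±10 (specificity) around accuracy at the optimal cut-off, labelled as resting on assumed distributions.

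**Statistical methods {20a}.** For every cut-off chosen from the data, report optimism-corrected sensitivity and specificity, with 95% intervals from a bootstrap that re-selects the cut-off in each resample. Say which accuracy is the target. Give a bootstrap interval for each cut-off offered as a reference value.

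**Alternative.** Fix the primary ultrasound-positive rule before analysis. The ±5 calculation then applies to the primary result if its accuracy is near the assumed values, and the Youden cut-offs become exploratory.

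**Cost.** One or two sentences in each section, a bootstrap script, and a less favourable stated precision. No extra patients and no change to the examinations.
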